#### Pairwise comparisons

After summary statistics are analyzed, pairwise comparisons of success, or attendance, rates (absolute risk differences) will be performed between the following groups using Chi-square tests adjusting for multiple comparisons:Control vs. Fixed incentiveControl vs. Lottery incentiveFixed vs. Lottery incentive

Risk differences and risk ratios (i.e., relative risks), along with their 95 % confidence intervals, will be presented to assess whether any significant differences between groups exist. This analysis will address the first two research questions of whether financial incentives, and then the design of the incentive scheme have an impact on screening attendance.

Further analyses will be conducted to explore the third research question about whether the incentive schemes attract patients with a different socioeconomic or demographic status. Although groups will be checked after randomisation on the basis of demographic factors, an exploratory subgroup analysis will be performed for adjustment of treatment effect by accounting for the available demographic covariates listed above using a multivariate logistic regression analysis, and performing model selection using a backward stepwise removal process based on a 0.05 significance level; covariate-adjusted differences in success, or attendance, rates between treatment groups will be computed. Significant associations will be identified by those with *p*-values < 0.05, while possible trends toward significance will be identified from 0.05 ≤ *p*-values < 0.10. With anticipated relatively low success rates globally, resulting estimates from these subgroup analyses could be unstable [38, 39], hence affecting possible reliability of the estimates which is why we emphasize the *exploratory* subgroup analysis.

To answer the third research question, comparisons will also be made to those who are classified as regular ‘current’ attenders (i.e., those who have attended at least 2 appointments in the past 3 years) to assess possible differences through demographic covariates and secondary outcome data between regular attenders and non-attenders.

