### Study design and procedure

The study design will be a three-arm randomized controlled trial. The effect of two different types of financial incentives will be compared to a control group with no incentives. The list of eligible participants identified by 1st Retinal Screen Ltd will be randomized by the statistician (according to an anonymous identifier), prior to the start of the study. No personal information about participants will be shared by 1st Retinal Screen Ltd. For *n* eligible participants provided in the list, they will be indexed according to numbers generated at random with double precision, to avoid duplicates. Participants will then be sorted from smallest to largest according to this random index. Within the sorted list and using the 1.4:1:1 randomisation ratio, we will assign: (1) the lowest n/3.4 participants to the fixed incentive group; (2) the following n/3.4 participants to the probabilistic incentive group; and (3) the remainder of the participants to the control group. We will round n/3.4 to the closest integer, if needed. Participants will be sent a letter by 1st Retinal Screen Ltd inviting them to their appointment, however they will be able to reschedule this appointment once (by phoning a number given on the letter), and still be eligible for the incentive. The letter sent will be determined by the intervention condition to which participants are assigned; these are described below.

The study will take place at a DES clinic based within St Mary’s Hospital, Imperial College Healthcare NHS Trust, in London, UK. Dedicated clinics will be arranged for trial participants, and for each of the intervention groups, so that non-trial patients are not aware of incentives offered to trial patients, and so participants within different groups are not aware of the different incentive conditions. A researcher will be present at the screening sessions for the intervention groups, in order to be able to answer any questions about the incentive, and to give the cash incentive to those in the fixed incentive group. As there will be designated clinics for each intervention group, it will not be possible for the researcher or screener to be blinded to the group assignment. However, as attendance at the clinic is the primary outcome, the study results cannot be biased by the lack of blinding at this stage. The study procedure is shown in Fig. 1.

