### Measures

The primary endpoint is the proportion of invitees who attend screening in each incentive group. This anonymised information will be extracted from the Screening Service database. For those participants who attend their screening appointment, data on their screening outcome score will be collected, aggregated by intervention group.

Demographic information will be collected for all invited participants on age, deprivation score and distance from screening center. Age data will given in deciles, starting from the lowest eligible age of 16 (i.e. 16–25, 26–35 etc.) with those aged 86 years and over being in the highest category. Deprivation scores will be measured based on the Indices of Multiple Deprivation score [35], which is based on postcodes, and will use the address to which the invitation is posted. This data will be given in deciles to ensure participant confidentiality. Distance to screening site will be measured based on the straight-line distance between the address on the day of screening, and the screening site, rounded to the nearest kilometre. Baseline demographics will also be collected for: gender, years registered, and years since last attended screening.

If participants telephone the screening center to opt not to participate in screening, the reason(s) provided will be recorded.

In all groups, when patients arrive, the screener will ask them for any reasons why they have not attended their past few appointments, in order to see if there are differences between intervention groups, and to explore common barriers to attendance in this hard-to-reach group. Reasons given will be noted in a table containing common reasons for non-attendance, along with the intervention group assignment. The reasons suggested are those given by patients in some informal telephone research conducted by 1st Retinal Screen Ltd (shown in Table 1).

**Table 1 Tab1:** Suggested reasons for past non-attendance

Suggested reasons for non-attendance	
Forgot	
Didn't know had an appointment	
Didn't get round to coming	
Was out of the country	
Started experiencing problem with eyes	
Did not feel obviously had problems with eyes	
Couldn't get time off work	
Didn't understand why needed to be screened	
Thought optician did it	
Family commitments	
Too ill to attend	
Seen privately	
Problems with transport	
Do not consider themselves diabetic	
Under the care of Hospital Eye Services	
Other - please specify	

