### Sample size calculation

The primary endpoint is the proportion of the study group who attend their diabetic retinopathy screening appointment. As the study group will comprise patients who have not attended screening for at least two years, including some who have never attended, despite previous interventions to encourage them to attend, this is a very hard to reach population. Attendance in the control group is expected to be extremely low, such as a nominal 1 %. As the eligible study population also tends to be the sickest, with the greatest risk of having retinopathy, and of losing their sight, even a small increase in attendance would have clinical and social benefit.

An increase in attendance of 10 % was deemed clinically significant. A 10 % increase was also considered achievable, as a study found that smoking cessation rates among employees of a large company increased from 5 % to 14.7 % with financial incentives [36], and in another study, warfarin adherence among subjects requiring anticoagulation management improved from 65 % to 97.8 % with a lottery based financial incentive [14]. With two intervention groups, each being compared to the control group, maximum statistical efficiency is achieved by randomising 1.4:1:1. Combining this with an assumed increase in attendance of 10 %, from 1 % in the control arm to 11 % in an intervention arm, there would be 95 % power if 1000 participants were recruited in total (412 in the control group, and 294 in each of the intervention groups). This sample size would also give the study at least 85 % power to detect a smaller increase from 1 % to 7.5 %, which would also be a clinically significant improvement in attendance rates. Should attendance in the control group turn out to be 5 %, the study would still have approximately 85 % power to detect an increase in attendance of 10 % to a level of 15 % in an intervention group [37].

Data from 1st Retinal Screen Ltd suggests that the study group could comprise over 1000 patients. This would allow oversampling at the randomisation stage, so that the intended sample size will still be reached even if participants become ineligible following randomisation (the most common reason for this is most likely to be due to participants attending their routine screening appointments).

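### The primary pairwise comparisons are valid but leave out time since last attendance, a planned baseline item; pre-specifying a stratified analysis would be a cheap, modest gain.

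*Protocol article*

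**What the plan says.** All references are to the protocol article.

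- **Primary comparisons** (Pairwise comparisons): "pairwise comparisons of success, or attendance, rates (absolute risk differences) will be performed between the following groups using Chi-square tests", with a multiplicity adjustment. For the estimates, "Risk differences and risk ratios (i.e., relative risks), along with their 95 % confidence intervals, will be presented". No covariate enters here, and the section ties this analysis to the first two research questions.
- **Allocation** (Study design and procedure): "Participants will then be sorted from smallest to largest according to this random index". The sorted list is then cut into the three groups. No stratification is described.
- **Population** (Sample size calculation): people without attendance for at least two years, "including some who have never attended".
- **The covariate** (Measures): "Baseline demographics will also be collected for: gender, years registered, and years since last attended screening".
- **Adjusted analysis** (Pairwise comparisons): a logistic regression on the listed covariates is planned for the third research question and will yield adjusted attendance differences. It is labelled exploratory, uses backward elimination at the 0.05 level, and carries a warning that low attendance may make its estimates unstable. Balance on demographics will also be checked after randomisation.

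**The concern.** Someone just over two years lapsed and someone who has never attended may respond quite differently to another invitation. If so, part of the variance of the crude risk difference comes only from how these people happen to be split between arms, and conditioning on a variable fixed before allocation removes that part.

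The exploratory model does not do this job. It serves another research question, its selection step may discard the variable, and the protocol itself doubts its stability. If the balance check shows uneven arms, no dependable adjusted estimate has been named in advance, and any decision to adjust would look post hoc. At stake are a little precision and a clear answer to that situation.

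**Working it through.** **Inputs from the document.** Arm sizes: "412 in the control group, and 294 in each of the intervention groups". Rates and power: "from 1 % in the control arm to 11 % in an intervention arm, there would be 95 % power". No significance level is given with the power figures, so I use two-sided 0.05 and, for three comparisons, 0.05/3 = 0.0167.

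**Assumptions.** The share of never-attenders and the strength of the predictor are not given. I take about half as never-attenders and, within an incentive arm averaging 11%, attendance of 14% vs 8%, 18% vs 4%, or 20% vs 3% in the two strata (odds ratios about 1.9, 5.3 and 8.1). The last pair averages 11% with 47% in the higher stratum.

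**1. The plan's own figure.** There is none on this covariate. The nearest is 95% power for 1% vs 11%. A pooled-variance normal approximation with 412 and 294 gives 99.98% at 0.05 and 99.92% at 0.0167. The stated 95% is not reproduced. That is a separate matter; here it shows only that this comparison has power to spare.

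**2. Standard error of the crude difference (1% vs 11%).**
√(0.01×0.99/412 + 0.11×0.89/294) = √(0.0000240 + 0.0003330) = 1.89 points. The incentive arm supplies 0.0003330/0.0003570 = 93% of the variance.

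**3. Share of the incentive arm's variance lying between strata**, f(1−f)(a−b)²/[p(1−p)], with p(1−p) = 0.0979:
- 14% vs 8%: 0.0009/0.0979 = 0.9%
- 18% vs 4%: 0.0049/0.0979 = 5.0%
- 20% vs 3%: 0.0072/0.0979 = 7.4%

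**4. Chance imbalance.** The difference between arms in the share of never-attenders has SD √[0.25×(1/412 + 1/294)] = 3.8 points. Multiplying by 14 points gives 0.53 point, but that applies a 14-point gap to the control arm too. With 1% control attendance and equal strata, the control gap cannot exceed 2 points (2% vs 0%). The variance of the shift is then at most 0.25×0.14²/294 + 0.25×0.02²/412 = 0.0000167 + 0.0000002 = 0.0000169, an SD of 0.41 point. As a share of the crude variance this is 0.41²/1.89² = 4.7%, which is the precision gain of step 3 carried to the difference. Removing it takes the standard error from 1.89 to 1.84 points.

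**5. A second parametrisation.** One binary factor with odds ratio 2 to 5 and prevalence 30% or 50%, using the variance of the standardised risk difference, gives these ratios of adjusted to crude variance and powers at two-sided 0.05:

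| Scenario | Variance ratio | Power, crude → adjusted |
|---|---|---|
| 1% vs 11% | 0.959–0.993 | 99.96% → at most 99.97% |
| 1% vs 7.5% | 0.969–0.995 | 98.1% → 98.1–98.4% |
| 5% vs 15% | 0.937–0.989 | 98.95% → 99.0–99.3% |

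At 0.0167 the largest gain is 96.95% → 97.8% (5% vs 15%). These savings are smaller than in step 3 partly because this variance also counts variation of the risk difference between strata. For 18% vs 4% with the 2-point control gap, that term is 0.25×(0.14−0.02)²/706 = 0.0000051, so the net saving is (0.0000169 − 0.0000051)/0.0003570 = 3.3%.

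**6. Outside the protocol's scenarios.** At 5% vs 11% the most favourable case (odds ratio 5, prevalence 30%) gains 2.0 points at 0.05 (80.9% → 82.9%). For fixed vs lottery the article states no power. Assuming 11% vs 15% with 294 per arm, crude power is about 30% at 0.05 and 17% at 0.0167; a variance cut of 5 to 7% adds about 1 to 2 points.

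**The case against.** The strongest reply is that nothing here is wrong. Chi-square tests with risk differences and risk ratios are valid under this randomisation, and their error rate and intervals already allow for chance imbalance. That stands in full.

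The reply continues that the covariate is not overlooked, since adjusted differences are planned and kept exploratory for a stated reason. With 412 × 0.01 ≈ 4 control attenders expected, caution about a multi-covariate regression is sensible. This stands in part. The adjusted analysis exists, but it neither guarantees that the variable is kept nor serves the primary comparisons. Mantel-Haenszel methods fit no regression coefficients and tolerate sparse strata, so the stated instability does not rule them out.

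Three stronger readings are tempting and unsupported:

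- A reader might infer that the crude estimates are biased. They are not; only some efficiency is given up.
- A reader might infer that time since last attendance is a strong predictor. The article gives no association and no share of never-attenders, and everyone eligible has already gone two years without attending.
- A reader might count precision and protection against imbalance as two benefits, or put the typical shift at 0.5 point. Step 4 shows one benefit, with an SD of about 0.4 point.

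**Conclusion.** The point holds as an optional, low-cost improvement. The primary comparisons are sound but unadjusted, allocation is unstratified, and a planned baseline variable that may be prognostic is left to an exploratory model that may drop it.

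The gain is modest: about 0.5 to 7% of variance across the assumed strengths, and less than 1 point of power for control versus incentive in the three scenarios the protocol gives. If the predictor is weak the gain is close to nil. No conclusion of the trial is likely to turn on it. For fixed versus lottery, where power is not stated and may be low, the gain is still only about 1 to 2 points under the assumed rates, so stratification would not rescue that comparison.

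**What to change.** Before the dataset is extracted, amend the pairwise analysis so that:

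- the primary test for each pair is Cochran-Mantel-Haenszel, with the Mantel-Haenszel risk difference and risk ratio and their confidence intervals;
- strata are a small number of pre-set bands of time since last attendance, measured at randomisation, with a separate never-attended category (for example 2–3 years, more than 3 years, never);
- the planned adjustment for multiple comparisons is kept;
- the crude chi-square, risk difference and risk ratio are reported as the sensitivity analysis.

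The cost is a few sentences of analysis wording. It needs no new data item and no change to invitations or clinics. The downside is that the bands must be fixed without sight of the data. The rule for coding never-attenders must also be settled with the data manager first, because the article does not say how years since last attendance is recorded for them.

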**Methods:**

This is a three arm randomized controlled trial to investigate the impact of different types of financial incentives (based on principles from behavioral economics) on increasing attendance at diabetic eye screening appointments in London. Eligible participants will be aged 16 or over, and are those who have been invited to screening appointments annually, but who have not attended, or telephoned to rearrange an appointment, within the last 24 months.

Eligible participants will be randomized to one of three conditions:Control condition (usual invitation letter)Fixed incentive condition (usual invitation letter, including a voucher for £10 if they attend their appointment)Probabilistic incentive condition (invitation letter, including a voucher for a 1 in 100 chance of winning £1000 if they attend their appointment).

Participants will be sent invitation letters, and the primary outcome will be whether or not they attend their appointment. One thousand participants will be included in total, randomized with a ratio of 1.4:1:1. In order to test whether the incentive scheme has a differential impact on patients from different demographic or socio-economic groups, information will be recorded on age, gender, distance from screening center, socio-economic status and length of time since they were last screened. A cost-effectiveness analysis will also be performed.

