### Research questions

In this study we will compare two different incentive schemes for diabetic retinopathy screening, with a usual-care control group, to determine:Are incentives an effective strategy to encourage participation in the screening programme?While screening for diabetic retinopathy is an effective strategy for reducing blindness, to be cost-effective the screening programme requires good attendance. However, attendance rates could be improved. This study will investigate whether targeted financial incentives can increase screening participation.Does the design of the financial incentive scheme affect its effectiveness in influencing participation in health screening?There are many ways in which incentives to encourage screening participation could be delivered. Two different types of financial incentive will be compared to see which is most effective: a fixed £10 incentive, or a prize draw with a 1 in 100 chance of winning £1000.Does the choice of incentive scheme, if successful, attract patients who have a different demographic or socioeconomic status to those who attend screening regularly?A particular concern is that those in deprived socio-economic groups are less likely to attend screening [7, 30], exacerbating existing inequalities in health. By investigating the impact of our incentive schemes on the demographic profile of those who attend, we hope to learn more about the way in which incentives might be developed to target specific health inequalities. We will obtain information about age, gender, postcode and hence social deprivation status, and distance from screening center.Is offering incentives a cost-effective strategy for enhancing participation?In the current financial environment it is also important to ensure that any interventions are cost-effective. Economic evaluation using well-established economic models will be performed to determine value for money.

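### The abstract aims to test differential impact across groups, but the model fixed for research question 3 is an adjustment model that names no arm-by-covariate term

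*Protocol article*

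**What the plan says.** **Aim.** The abstract (Methods) gives the reason for recording age, gender, distance, socio-economic status and time since last screening: "In order to test whether the incentive scheme has a differential impact on patients from different demographic or socio-economic groups". Research question 3 is worded differently: "Does the choice of incentive scheme, if successful, attract patients who have a different demographic or socioeconomic status to those who attend screening regularly". Its explanatory text refers to existing health inequalities and to targeting them.

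**Analysis.** The section Pairwise comparisons opens this part with "Further analyses will be conducted to explore the third research question about whether the incentive schemes attract patients with a different socioeconomic or demographic status". It then sets out a logistic regression:
- Purpose: "an exploratory subgroup analysis will be performed for adjustment of treatment effect by accounting for the available demographic covariates listed above".
- Choice of terms: "performing model selection using a backward stepwise removal process based on a 0.05 significance level".
- Output: "covariate-adjusted differences in success, or attendance, rates between treatment groups will be computed".

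A second analysis for the same question brings in people who attend regularly, "to assess possible differences through demographic covariates and secondary outcome data between regular attenders and non-attenders".

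**Related text.** Summary statistics promises attendance counts and proportions by treatment group and demographics. Cost-effectiveness analysis says the research question 3 analysis will show whether the incentives are associated with individual characteristics. If they are, and the literature shows that the significant characteristics affect costs or quality of life, this enters the long-term model.

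**The concern.** A differential impact means that the difference between arms varies with the covariate. That is an arm-by-covariate quantity. A model for adjusting the treatment effect, reporting adjusted differences between arms, answers another question: what is the arm effect once covariates are accounted for? The coefficient of deprivation in such a model says whether deprived people attend more or less overall, not whether the incentive moves them more or less.

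Two errors can follow. A covariate that only predicts attendance may be kept and read as a group to whom the incentive appeals. A covariate that raises the effect of one scheme and lowers that of the other may show little overall association and be dropped by the 0.05 rule. Either error can pass into the economic model, which takes its list of characteristics from this analysis. Whether incentives narrow or widen inequality is the concern behind one of the four research questions.

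**Working it through.** **Inputs from the protocol article.** Arms of 412/294/294 (1000 × 1.4/3.4 = 411.8; 1000/3.4 = 294.1), and planning rates of 1% vs 11% and 5% vs 15% (Sample size calculation). The article gives no power figure for research question 3, so there is none to reproduce.

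**Events available.** 0.01 × 412 + 0.11 × 588 = 68.8 attendances in the first scenario, about 4 of them in control. 0.05 × 412 + 0.15 × 588 = 108.8 in the other.

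**What a model without the interaction returns.** Assume one incentive arm against control, a binary covariate split 50:50 (206 per half in control, 147 in the incentive arm), and control attendance of 1% in both halves. Fitting expected counts gives:

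| Incentive-arm attendance, two halves | Arm log-OR, no interaction | Covariate log-OR, no interaction | Interaction log-OR when included |
|---|---|---|---|
| 11% / 11% | 2.504 | 0 | 0 |
| 6% / 16% | 2.524 | +0.944 | +1.093 |
| 16% / 6% | 2.524 | −0.944 | −1.093 |

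The arm coefficient is identical under opposite patterns. In the 6%/16% case the fitted values without interaction are 0.6%/1.4% in control and 6.6%/15.4% in the incentive arm. A covariate that is only prognostic on the logit scale would give that same fit, so the covariate coefficient does not separate the two explanations.

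**Precision of the interaction in that example.**
- Logit scale: estimate = logit(0.16) − logit(0.06) = 1.093, because the control terms cancel. SE = √[Σ 1/(n p(1−p))] over the four cells = 1.073. Two-sided 5% power = Φ(1.093/1.073 − 1.96) = 17%.
- Risk-difference scale: variance = 2(0.01 × 0.99)/206 + (0.06 × 0.94)/147 + (0.16 × 0.84)/147 = 0.00139, SE = 0.0373. Power = Φ(0.10/0.0373 − 1.96) = 76%.
- Control 5% and incentive arm 10%/20%: 30% (logit) and 58% (risk difference).

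**Three-arm simulations.** 412/294/294, deprivation decile as a linear score, logit scale, 500 or 600 trials per run (Monte Carlo standard error at most √(0.25/500) = 2.2 points). All gradients are assumptions. Control is flat.

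| Assumed attendance across deciles | Deprivation main term, p < 0.05 | 2-df arm-by-deprivation, p < 0.05 |
|---|---|---|
| Fixed 4%→18%, lottery reversed, control 3% | 4–5% | 88–90% |
| Same, control 1% | 5.5% | 91% |
| Opposite but milder (7%→15%), control 3% | 7% | 42–43% |
| One scheme 4%→18%, other flat at 11%, control 1% | 42% | 37% |
| Both schemes 4%→18%, control 1% | 93% | 12% |
| Both schemes 4%→18%, control 3% | 89% | 25–27% |

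With opposite gradients the main term is significant at roughly the chance rate, so backward removal would nearly always drop deprivation. With a shared gradient the main term is usually retained, but it does not itself show that the incentive effect differs.

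**The case against.** **The text never says main effects only.** True. It uses the label subgroup analysis, and the exact terms may stand in an analysis plan that is not shown. A reader might infer that the plan rules out any look at effect modification; the article does not go that far. What stands is that the purpose and output it does state are adjustment, and that it names no interaction for the aim in the abstract.

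**Opposite patterns would not stay hidden.** The table by treatment group and demographics would display them, so it does not follow that the trial would report no socio-economic difference. But no test or interval for a difference in effect is specified for that table.

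**The contrast of about 4% with about 90% is a best case.** Correct. It relies on exactly mirrored gradients, where the main term cancels by construction. When both schemes favour the same group, the interaction test on the logit scale usually misses it.

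**The regular-attender comparison answers research question 3 as worded.** It does address those words, and a difference between non-attenders and regular attenders is part of the subject. The comparison is not invalid. The narrower gap is that the text contrasts regular attenders with non-attenders, and not with those who attend in each arm.

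**Backward removal and the 0.05–0.10 trend band.** A reader might infer that the band can never be used, since such covariates are removed. The article does not restrict it to retained covariates; it could apply to arm contrasts or to the regular-attender comparison.

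**The analysis is labelled exploratory and warned to be unstable.** That covers imprecision. It does not turn an adjustment model into an estimate of effect modification.

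**Conclusion.** The concern holds as a mismatch between a stated aim and the analysis the article itself fixes for it. The abstract promises a test of differential impact; the model assigned to research question 3 is for adjustment, selects covariates by significance, and reports adjusted arm differences. Without an arm-by-covariate term, opposite patterns give the same arm coefficient and a retained covariate may be merely prognostic. The consequence reaches the economic analysis, which treats this result as showing an association between the incentives and individual characteristics.

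The size depends on gradients the documents do not give. In the assumed cases, interaction power runs from about 12% (both schemes graded the same way, logit scale) to about 90% (strong, exactly opposite gradients). The documents do not support the stronger conclusion that the trial could not reveal any differential pattern. The pairwise tests for research questions 1 and 2 are unaffected. The change should be made, but it is not critical to the primary result.

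**What to change.** 1. Prespecify arm-by-deprivation as the first interaction, with decile as a linear score, then a short fixed list: age band, distance, sex.
2. Report each interaction with its 95% confidence interval on the risk-difference and logit scales, beside attendance by arm across the covariate. Both scales are needed because a covariate that is only prognostic on the logit scale still gives unequal risk differences (in the illustration about 15.4 − 1.4 = 14 points against 6.6 − 0.6 = 6).
3. In the adjusted model keep arm and all listed covariates, in place of backward elimination.
4. Base the step in Cost-effectiveness analysis on these interaction estimates, not on covariates that happen to be significant.
5. Make the regular-attender comparison one of attenders in each arm against regular attenders, as description.

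The cost is a change of analysis wording and a few extra models on data already to be collected. The downside is imprecision: with about 4 control attendances expected at 1%, the interactions remain exploratory, and the report should say that a non-significant interaction is not evidence of equal effect.
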